Safety endpoints: health outcome and safety data are closely monitored and collected throughout the infant’s stay until discharge or death. Infant safety is being assessed through the monitoring for adverse events by the Data Safety and Monitoring Board (DSMB), comprised of independent reviewers. The DSMB meets every 6 months during the first year of active enrollment, and thereafter at ¼, ½ and ¾ enrollment to ensure rapid identification of adverse events. Adverse events are defined to include aspiration, significant bradycardia following (oropharyngeal milk) administration leading to the need for resuscitation, and post-natal acquisition of cytomegalovirus (CMV) thought to be associated with fresh milk. Studies have identified the potential risk of milk-acquired CMV infection, but based on the small volumes and controversial risk (even with frozen milk), we promote fresh milk as our standard in this study, as we did with our pilot studies, and follow clinically for symptoms of acquired CMV and will intervene quickly if a case should arise. To maintain safety of enrolled infants, vital signs are carefully monitored during the oropharyngeal administration of the study substance (milk or sterile water). The nurses are instructed to immediately stop the procedure and to notify the site PI if any of the following signs of aspiration should occur: an increase in fraction of inspiratory oxygen > 0.1 to maintain a SpO_2_ > 85 %, bradycardia (heart rate (HR) < 100/minute), tachycardia (HR > 200/minute), tachypnea (respiratory rate (RR) > 80/minute), or apnea. Treatments are withheld during surgical and invasive procedures or based on clinical evidence of acidosis, NEC, multisystem organ failure, or other instances of clinical deterioration, but this decision is left to the discretion of the attending physician after discussion with the site PI (another neonatologist).

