##### Statistical analysis

Statistical analysis will be performed using an intention-to-treat (ITT) approach. Baseline infant and mother demographics and clinical characteristics will be summarized between milk and placebo groups using a chi-square or Fisher exact test for categorical variables (i.e. infant gender, race/ethnicity, socioeconomic status, maternal diagnosis of pre-eclampsia, premature and/or prolonged rupture of membranes, delivery mode, and steroid administration) and an independent *t* test or a Wilcoxon two-sample test for continuous variables (i.e. the time of initial exposure to mother’s own milk, duration [number of days] of central line placement and mechanical ventilation, gestational age, birth weight, post-natal steroids, antibiotic duration), depending on satisfying the normality assumption or not, respectively. A multivariable logistic regression with L-OS or NEC or death as the dependent variable, and group (milk versus placebo) as the primary independent variable will be constructed to assess the strength of association between oropharyngeal milk treatment and risk of L-OS or NEC or death, adjusting for pre-specified covariates including sex, gestational age and birth weight. Odds ratios and corresponding 95 % confidence intervals will be reported. Because the amount of mother’s milk that enrolled infants receive as a “feeding” will affect our study endpoints, we will closely monitor and record the total amount of mother’s milk received (percent of total feeding volume) for each study subject. We do not anticipate the amount of milk the infant receives as an enteral feed will be affected by group assignment. However, if we do observe a significant difference between the intervention and placebo groups, we will control for this variable in the regression models. While the main hypotheses will be tested using ITT analysis, we will also conduct per protocol analysis only for patients who complete the treatment. Completed treatment is defined as (the infant) having received 70 % of planned doses. However, this will be considered supplemental and exploratory, and the results will not be used as main conclusions of the study.

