## Discussion

This multi-center, double-blind RCT was designed to evaluate the safety and efficacy of oropharyngeal administration of OMM to reduce the incidence of L-OS and NEC in a large cohort of extremely premature infants. For treated infants, we anticipate beneficial gastrointestinal effects (e.g. trophic effects on the intestine and a predominance of beneficial microflora), immunostimulatory effects (higher concentrations of urinary lactoferrin), enhanced antioxidant status (measured by changes in levels of urinary biomarkers of oxidative stress), and a decreased incidence of L-OS and NEC.

To date, 77 subjects have been enrolled. There have been 11 screen failures because consent was obtained antenatally (per protocol), but once the mother gave birth the infant’s weight was over 1250 g and he/she was no longer eligible for the study. The remaining 66 subjects have completed treatment. A total of 13,433 treatments have been administered to enrolled subjects, corresponding to a total of 26,866 syringes having been prepared. Importantly, subjects have received > 90 % of planned treatments; demonstrating strict adherence to the rigorous research protocol. For each infant, once enrolled, we carefully calculate the number of “planned doses” to be given. This calculation is based on the infant’s gestational age at birth and the date the infant will reach 32 weeks CGA. On a daily basis, we track the number of treatments that are given. Each dose that is administered is documented in the infant’s intake flow-sheet, in the medication administration record, and also in a study-specific form. Bedside nurses are blind to group assignment and document the “dose” administered as “study substance.” At the completion of the extended treatment period, the percent of “planned doses” that were actually given, is calculated and recorded. Completed treatment is defined as (the infant) having received 70 % of planned doses.

All doses have been well-tolerated by enrolled infants and no adverse effects have been reported. Infant safety is carefully assessed as described in the previous section.

We are recruiting infants from five large tertiary neonatal centers. We anticipate a racially, ethnically and economically diverse cohort, with broad representation of medically underserved women and minorities, and sufficient numbers from which to recruit and test our aims.

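### The exploratory per-protocol set counts doses against a total running to 32 weeks CGA, so early deaths, and infants with long clinical holds, are excluded because of the outcome rather than poor adherence

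*Protocol article*

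**What the plan says.** Under Statistical analysis, the article makes intention-to-treat the main approach and adds a second analysis: "we will also conduct per protocol analysis only for patients who complete the treatment". The entry rule follows: "Completed treatment is defined as (the infant) having received 70 % of planned doses". The Discussion repeats that rule and explains how the planned number is obtained once an infant is enrolled: "This calculation is based on the infant’s gestational age at birth and the date the infant will reach 32 weeks CGA". The percentage actually given is worked out when the extended treatment period ends. Nothing is said about an infant who dies before then, or about doses withheld for clinical reasons.

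The safety paragraph under Outcome measures for specific Aim 1 lists reasons for withholding: "Treatments are withheld during surgical and invasive procedures or based on clinical evidence of acidosis, NEC, multisystem organ failure", together with other clinical deterioration, at the attending physician's discretion. NEC and death are the secondary endpoints, and the planned model is "A multivariable logistic regression with L-OS or NEC or death as the dependent variable". The article limits the use of the per-protocol result: "this will be considered supplemental and exploratory, and the results will not be used as main conclusions of the study".

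**The concern.** Membership of the set is decided after randomization, by a count that death and NEC can themselves reduce. For early death the link is arithmetic: dosing stops, the denominator does not, and the infant is classed as a non-completer however good adherence was while alive. For NEC or deterioration the link runs through withheld doses and applies when the hold is long.

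A per-protocol analysis should show what happens in infants treated as planned. Here it would drop some infants treated exactly as planned because they had the outcome under study. Death, and possibly NEC, would look rarer than they were, and the comparison between arms would be distorted if the arms lost different shares of their events.

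**Working it through.** **Dose rate, checked against the article.** Two syringes make one treatment. The 24 syringes prepared for the first day give 24/2 = 12 treatments (every 2 hours); the 16 syringes a day later give 16/2 = 8 (every 3 hours). The Discussion's totals agree: 26,866/13,433 = 2 syringes per treatment.

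**Planned doses.** Let D be the days from first dose to 32 weeks CGA.
- Planned = 24 + 8 × (D − 2)
- Days from first dose to the 70 % point, none missed = 2 + (0.70 × planned − 24)/8
- Hold that uses up the 30 % allowance = 0.30 × planned/8 days

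The first dose is taken on day 1 or day 4, because dosing must start within 96 hours of birth. Gestational ages at birth are chosen for illustration.

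| Birth (weeks) | First dose (day) | D | Planned | 70 % of planned | Age at 70 % (day) | Hold allowance (days) |
|---|---|---|---|---|---|---|
| 24 | 1 | 55 | 448 | 313.6 | 39.2 | 16.8 |
| 24 | 4 | 52 | 424 | 296.8 | 40.1 | 15.9 |
| 26 | 1 | 41 | 336 | 235.2 | 29.4 | 12.6 |
| 26 | 4 | 38 | 312 | 218.4 | 30.3 | 11.7 |
| 28 | 1 | 27 | 224 | 156.8 | 19.6 | 8.4 |
| 28 | 4 | 24 | 200 | 140.0 | 20.5 | 7.5 |
| 30 | 1 | 13 | 112 | 78.4 | 9.8 | 4.2 |
| 30 | 4 | 10 | 88 | 61.6 | 10.7 | 3.3 |

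**Example.** An infant born at 26 weeks starts on day 1, misses nothing and dies on day 20, 19 days after the first dose. Doses given = 24 + 8 × 17 = 160. Against the planned total this is 160/336 = 48 %, so the infant is excluded. Against doses due while alive it is 160/160 = 100 %.

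**Typical infant so far.** 13,433/66 = 203.5 doses each. With more than 90 % of planned treatments given, planned doses average at most about 203.5/0.9 = 226, close to the 28-week row. The 30 % allowance is then about 68 doses, or 8.5 days of 3-hourly dosing.

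**Effect on absolute risk (assumed inputs).** If a share f of infants with the event is removed and no event-free infants are, a risk p becomes p(1 − f)/(1 − pf). The article gives no death risk or timing of deaths, so p = 5-15 % and f = 50-80 % are assumptions:
- p = 5 %: 1.0-2.6 %
- p = 10 %: 2.2-5.3 %
- p = 15 %: 3.4-8.1 %

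With 622/2 = 311 infants per arm, between 311 × 0.05 × 0.5 ≈ 8 and 311 × 0.15 × 0.8 ≈ 37 deaths per arm would be removed.

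**Effect on the odds ratio.** Under the same simplification, the odds ratio is multiplied by (1 − f_milk)/(1 − f_placebo).
- Equal shares: no change. A true 0.44 stays 0.44.
- 70 % removed in milk, 50 % in placebo, no true effect: 0.30/0.50 = 0.60.
- 80 % and 40 %: 0.20/0.60 = 0.33.

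These shares show the mechanism; they are not estimates for this trial.

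**The case against.** The strongest reply is that the authors have already contained the problem. Intention-to-treat carries the main hypotheses, the per-protocol result is declared exploratory, and any completer set conditions on post-randomization behaviour. That stands, and it limits the consequence. It does not make the result interpretable if it is reported.

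A second reply is that the article is silent on how deaths and holds enter the denominator, and that a fuller document may settle it. The silence is real. But the article fixes both the cut-off and the basis of the planned count, and those two rules taken as written exclude early deaths.

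A third is that all 66 infants dosed so far are described as having completed treatment. If the 70 % rule was used for that statement, nobody has yet been lost. It does not change what the rule does to a later early death.

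A reader might also infer more than the text supports:
- **That any hold for NEC or deterioration removes the infant.** Only a loss of more than 30 % of planned doses does. The article gives no hold durations, so the number affected is unknown.
- **That the late-onset sepsis comparison loses its sickest cases.** Sepsis is not a named reason for withholding; it could enter only through general deterioration.
- **That the rule selects on lactation in the milk arm alone.** The article does not say whether water continues once a mother stops pumping, and its 20 % dropout allowance is not arm-specific.
- **That the per-protocol odds ratio must be biased.** Removal of equal shares of events leaves it unchanged in the calculation above.

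**Conclusion.** The concern holds for the exploratory per-protocol analysis only. As written, every death before the 70 % point is excluded whatever the adherence: about day 39-40 for births at 24 weeks, 29-30 at 26 weeks, 20 at 28 weeks and 10-11 at 30 weeks, assuming a first dose on day 1-4 and none missed. Missed doses push the point later. Holds exclude an infant only when long, roughly 16-17, 12-13, 7.5-8.4 and 3.3-4.2 days at those four gestational ages if nothing else is missed.

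The per-protocol death risk is understated in both arms, provided the rule removes a larger share of deaths than of survivors. NEC may be understated too. Bias in the odds ratios depends on a difference between arms in the share of events removed, which the article gives no means to estimate. The intention-to-treat conclusions and the sample size are not affected.

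**What to change.** For the per-protocol set only:
- Define adherence as doses given divided by doses due from the first dose until the earlier of 32 weeks CGA or death.
- Do not count doses withheld under the article's own withholding provision as missed.
- Keep the 70 % cut-off.
- Report the number excluded, with reasons, by arm.
- Show truncation at first late-onset sepsis or NEC as a sensitivity analysis only, because it makes the adherence window depend on the endpoint.

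The cost is a changed definition and a recalculation from the daily dose record. Truncation at death needs only dates. Setting holds aside needs the reason for each withheld dose, and the article does not say whether that is recorded. The revised set will include some infants with short exposure. It remains a post-randomization selection, so it should stay exploratory. No dosing or withholding rule changes.

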##### Analysis of safety endpoints

Safety endpoints will be analyzed using summary statistics (frequency, count, percent). We will compare each safety endpoint between milk and placebo groups using chi-square and Fisher exact tests. We will also analyze the safety endpoint count data by conducting Poisson regressions using group (milk versus placebo) as the independent variable, controlling for covariates described above if applicable.

##### Outcome measures for specific Aim 2

This is an exploratory aim of the trial and, therefore, should not be considered as the primary endpoint of the study. We hypothesize that oropharyngeal administration of OMM will modulate microbiome, antioxidant status and urinary lactoferrin concentrations for recipient infants. These measures are described below.

##### Microbiome

We hypothesize that mother’s milk will modulate fecal microbiota of extremely premature infants leading to increased microbial diversity with a *Lactobacillus/Bifidobacterium* predominance and decreased *Proteobacteria*. Samples of milk, oral mucosa swabs, and stool are collected at the time of first stool, 2 weeks of age and at 32 weeks CGA for enrolled subjects and frozen immediately at −80 °C. For subjects who develop L-OS or NEC an additional stool sample is obtained at the time of diagnosis, and results correlated with the 32 -week samples. The composition and structure of the microbiome from milk, oral mucosa, and stool will be tracked using high-throughput 16S rRNA-based gene analysis as per previously published protocols [20, 82].

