NEC, like L-OS, is associated with significant mortality and long-term morbidities for extremely premature infants. NEC is an inflammatory bowel necrosis which involves mucosal injury, altered intestinal microbiota, an unbalanced pro-inflammatory response, and abnormal host defense [4]. NEC is common in extremely premature infants because they have an immature intestinal epithelial barrier that is vulnerable to injury, a gastrointestinal microbiota which has a predominance of potential pathogens, an unbalanced pro-inflammatory response to pathogenic bacteria by immature enterocytes, decreased tight junctions between epithelial cells (permitting the translocation of pathogens) and an immature host defense system [4, 5, 13].

Pathogenic colonization of the preterm gut appears to be a primary step in the pathogenesis of both L-OS and NEC [5, 13, 19–21]. A pathogen-predominant microbiota promotes injury to the mucosal barrier and facilitates bacterial translocation from the gut into the bloodstream [22]. Recent research suggests that specific pathogens colonize the preterm gut before they invade the bloodstream with subsequent L-OS, confirming the importance of abnormal microbiota with subsequent mucosal translocation as an important pathomechanism [22, 23]. Therefore, optimizing the intestinal microbiome in extremely premature infants could reduce the risk of L-OS, and also NEC. Methods to enhance beneficial bacteria and improve microbial diversity may decrease the risk for L-OS and NEC via multiple mechanisms. Exposure to mother’s milk post-birth can reduce colonization by pathogenic organisms and increase commensal bacteria, reducing bacterial translocation, modulating the inflammatory response and decreasing intestinal injury [24–27].

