## Methods/Design

### Study design

This study is a 5-year, prospective, double-blind, placebo-controlled randomized clinical trial across 5 large neonatal centers, designed to evaluate the safety and efficacy of oropharyngeal administration of own mother's milk to reduce the incidence of L-OS, and NEC and death, in a large cohort of extremely premature infants (*n* = 622; total patients enrolled). A multi-center 5-year trial is necessary in order to reach the target sample, based on average numbers of extremely premature infants admitted yearly to participating sites. Enrolled infants are randomized to one of 2 groups using computer-generated random numbers: Group A (treatment) infants receive 0.2 mL of own mother’s milk (OMM) via oropharyngeal administration every 2 hours for an initial treatment period of 48 continuous hours, followed by an extended treatment period of 0.2 mL of OMM via oropharyngeal administration every 3 hours until 32 weeks CGA. Group B infants (control) receive a placebo (sterile water, and blinded as described below) using the same dose and following the same protocol. Samples of mother’s milk and infant’s urine are collected at baseline and within 6 hours after the completion of the Initial Treatment Period and the Extended Treatment Period. A sample of infant’s urine is collected at 7 days of life. Milk, oral mucosal swab, and stool samples are collected at the time of first stool, 2 weeks of life and at 32 weeks CGA. For infants diagnosed with L-OS or NEC, a stool sample is collected at the time of diagnosis. Health outcome and safety data are closely monitored and collected throughout the infant’s stay until discharge or death. See Fig. 1 for the timeline of the study.

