Primary endpoints: L-OS is defined as the new onset of at least 2 clinical symptoms with a positive blood culture (noted after Day of life 3) and identification of an organism known to be a cause of sepsis rather than a contaminant. If the blood culture shows a potential contaminant (such as *Staphylococcus epidermidis*) a second blood culture is obtained to confirm the presence of bacteremia.

Secondary endpoints: NEC and death. NEC is defined according to modified Bell’s criteria stage > 2 with clinical signs and radiological evidence including any of the following: pneumatosis intestinalis, portal venous gas with or without pneumoperitoneum.

Covariates: sex, gestational age and birth weight will be included as covariates.

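### The stool taken at L-OS or NEC diagnosis is paired only with the 32-week stool, which follows the event when disease occurs before 32 weeks and precedes it otherwise, so the named correlation mixes pairs of opposite time order

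*Protocol article*

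**What the plan says.** The Study design section of the protocol article adds an event-driven specimen to the schedule: "For infants diagnosed with L-OS or NEC, a stool sample is collected at the time of diagnosis". The Microbiome section, under the outcome measures for Aim 2, repeats this and states the comparison: "an additional stool sample is obtained at the time of diagnosis, and results correlated with the 32 -week samples". That is the only comparator named for the diagnosis stool.

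The same section sets the routine schedule, in which milk, oral swabs and "stool are collected at the time of first stool, 2 weeks of age and at 32 weeks CGA for enrolled subjects". It also says: "The composition and structure of the microbiome from milk, oral mucosa, and stool will be tracked using high-throughput 16S rRNA-based gene analysis". Its hypothesis begins "We hypothesize that mother’s milk will modulate fecal microbiota of extremely premature infants".

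On the order of events, the Background cites research suggesting that "specific pathogens colonize the preterm gut before they invade the bloodstream with subsequent L-OS". The Objectives section gives Aim 2 as identifying the biomechanisms behind any benefit of the milk. The opening of the Aim 2 outcome section limits the weight of all this: "This is an exploratory aim of the trial and, therefore, should not be considered as the primary endpoint of the study".

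**The concern.** A stool taken at diagnosis bears on one question in particular: what the gut flora looked like around the onset of disease, and how that relates to its state at another time. The mechanism set out in the Background has abnormal colonisation coming first and invasion second. A specimen from before the event can speak to that order. A specimen from after it cannot, because it also carries the effects of the disease, its treatment and further maturation.

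The article itself names influences of this kind. The Background lists antibiotic overuse among the factors that lower microbial diversity, and the safety section allows study doses to be withheld for NEC or clinical deterioration.

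If some pairs run from before the event to the event, and others from the event to after it, a single correlation over all of them has no single meaning. What is at stake is how to interpret one exploratory analysis that links milk, microbiota and infection.

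**Working it through.** The article gives no figure for this analysis, so there is nothing to reproduce. The check is of time order first, then of how many events could be affected.

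**1. Time order from the schedule** (for an infant who reaches 32 weeks CGA after 2 weeks of age)

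| Time of event | Last scheduled stool before it | 32-week stool relative to event |
|---|---|---|
| Before 2 weeks of age | First stool | After |
| From 2 weeks of age to 32 weeks CGA | 2-week stool | After |
| After 32 weeks CGA | 32-week stool | Before |
| Any event, death before 32 weeks CGA | First or 2-week stool | Does not exist |

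The first two rows and the third have opposite time order. The fourth gives no observed pair.

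**2. When 32 weeks CGA falls for an average infant**

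Inputs from the Discussion: 13,433 treatments, 66 infants who completed treatment, more than 90% of planned treatments received. Dosing is every 2 hours for 48 hours (24 doses), then every 3 hours (8 per day). The first dose is given within 96 hours of birth.

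- Treatments per infant: 13,433 / 66 = 203.5.
- Planned treatments, if between 100% and 90% were received: 203.5 to 203.5 / 0.9 = 226.1.
- Days on protocol = 2 + (planned − 24) / 8: from 2 + 179.5 / 8 = 24.4 to 2 + 202.1 / 8 = 27.3.
- Adding 0 to 4 days before the first dose, 32 weeks CGA falls at about day 24 to 31 of life.

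**3. Share of events before that day**

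L-OS requires a "positive blood culture (noted after Day of life 3"). Outcomes are collected to discharge or death, and the Background gives a typical stay of 12 to 17 weeks, that is 84 to 119 days. *Assumption:* constant hazard, so events are spread evenly from day 3 to discharge.

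Share = (day of 32 weeks − 3) / (day of discharge − 3)

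- Lowest: (24 − 3) / (119 − 3) = 21 / 116 = 18%.
- Highest: (31 − 3) / (84 − 3) = 28 / 81 = 35%.
- Very immature infant who reaches 32 weeks at day 56 (*assumption*): 53 / 116 = 46% to 53 / 81 = 65%.

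**4. What it would take for most events to come first**

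For an average infant, more than half of events precede the 32-week stool only if the earlier hazard exceeds the later one by a factor of (discharge − day of 32 weeks) / (day of 32 weeks − 3). This runs from (84 − 31) / 28 = 1.9 to (119 − 24) / 21 = 4.5.

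**5. In numbers of infants**

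At the planning rates, L-OS cases among the 498 analysed would be 249 × 0.20 + 249 × 0.10 = 74.7. Applying 18.1% and 34.6% gives about 14 to 26 L-OS infants whose 32-week stool would follow the event. NEC cases would add to this, but the article gives no timing for them either.

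**6. Is an earlier stool available?**

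Under the same assumption, the share of pre-32-week events that fall after the 2-week stool is (day of 32 weeks − 14) / (day of 32 weeks − 3): 10 / 21 = 48%, 17 / 28 = 61%, and for day 56, 42 / 53 = 79%. For the remainder, only the first stool precedes the event.

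**The case against.** The strongest reply is that this is one clause, in an article that condenses a longer protocol, about an aim labelled exploratory. The stated hypothesis concerns the effect of milk on the microbiota. Colonisation before invasion is background, not something the Microbiome section promises to test with the diagnosis stool. First and 2-week stools are collected from all enrolled infants and the microbiome is to be tracked, so the trial does hold pre-event data and nothing forbids using them. The clause is also ambiguous: it may mean the infant's own 32-week stool or those of unaffected infants.

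Much of this stands, and it rules out several stronger readings that a reader might infer:

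- *That the 32-week stool usually follows the event.* The article gives no event timing. Under even spread, most events in an average infant would come after that stool, which is then a valid pre-event sample. Early clustering is plausible, since the Background ties L-OS risk to central lines and parenteral nutrition, but no figure shows it.
- *That the direction of cause is reversed.* A correlation asserts no direction. Only the time order is reversed, and only for events before 32 weeks.
- *That infants who die are dropped.* No exclusion is written. They cannot form this one observed pair, but their other samples remain usable. The general missing-data plan does not address a specimen that never existed, and no death rate before 32 weeks is given.
- *That the trial cannot address what came first.* This is true only of the named correlation.

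The reply does not rescue the comparator itself. The article does not leave the choice open; it names one, and Aim 2 does ask about mechanism. Nor does the second reading of the clause help: setting cases sampled at younger ages against unaffected infants at 32 weeks would mix age with disease.

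**Conclusion.** The point holds in a limited form. The one comparison stated for the diagnosis stool pools pairs of opposite time order and cannot by itself show whether abnormal microbiota preceded disease. It also rests, in its observed pairs, on infants who survive to 32 weeks.

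The time-order result follows from the sampling schedule alone. The size does not: 18 to 35% of events for an average infant depends on an assumed constant hazard and on a mean taken from the first 66 infants to complete treatment. The share is higher if events cluster early or the infant is very immature. In either case a material number of pairs is likely to lie on each side of 32 weeks.

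The weight is modest. The aim is exploratory, and the primary L-OS analysis and the sample size of 498 are untouched.

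**What to change.** Reword the clause on the diagnosis stool so that:

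1. The main comparator is the same infant's last scheduled stool before diagnosis: first stool, 2-week stool, or 32-week stool if the event comes later. This gives every pair the same time order and keeps infants who die before 32 weeks.
2. Cases are also compared with unaffected infants at the scheduled sample closest in age, with adjustment for gestational age.
3. 32-week stools taken after an event are used only to describe the later course.

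The cost is a change of wording; every specimen needed is already on the schedule. The downside is that events before the 2-week sample have only the first stool as a predecessor, so those pairs say less about the flora just before disease. They should be identified as such when results are reported.
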